## Abstract

**Background:**

Hearing and vision impairments are among the most common and disabling comorbidities in people living with dementia. Intervening to improve sensory function could be a means by which the lives of people living with dementia may be improved. However, very few studies have tried to ameliorate outcomes in dementia by improving sensory function. This paper describes the multi-step development of a new intervention designed to support hearing and vision function in people living with dementia in their own homes. At the end of the development programme, it is anticipated that a ‘sensory support’ package will be ready for testing in a full scale randomised controlled trial.

**Methods:**

This programme is based on the process of ‘intervention mapping’ and comprises four integrated steps, designed to address the following: (1) scoping the gaps in understanding, awareness and service provision for the hearing and/or vision impairment care needs of people with dementia using a systematic literature review and Expert Reference Group; (2) investigating the support care needs through a literature search, stakeholder surveys, focus groups, semi-structured interviews and an Expert Reference Group, leading to a prototype sensory support package; (3) refining the prototype by additional input from stakeholders using focus groups and semi-structured interviews; and (4) field testing the draft intervention using an open-labelled, non-randomised feasibility study, integrating feedback from people with dementia and their significant others to develop the final intervention ready for full scale definitive trialling. Input from the ‘patient and public voice’ is a cornerstone of the work and will interlink with each step of the development process. The programme will take place in study centres in Manchester, Nicosia and Bordeaux.

**Discussion:**

Quantitative and qualitative data analyses will be employed, dependent upon the sub-studies in question. Data from the steps will be integrated with consideration given to weighting of evidence for each step of the programme. This programme represents the logical development of a complex intervention to fulfil an unmet need. It is based on a theoretical framework and will lead to a subsequent full scale efficacy trial. The challenges in integrating the data and addressing the contextual issues across study sites will be scrutinised.

## Background

The purpose of this paper is to outline the steps we will take to develop a new intervention to support people with dementia and concurrent hearing and vision impairment living at home. The present research programme will shape the new intervention and its delivery structures, as *per* guidelines for the development of complex interventions [1] and the process of ‘intervention mapping’ [2].

### Hearing and vision impairment in dementia represents an unmet need

Hearing, vision and cognitive impairment are all within the top ten highest disease burdens in the European Union (EU) in terms of reduced quality of life and increased healthcare utilisation [3]. As people age, the incidence of developing one or more of these impairments rises dramatically, to the point whereby seven in ten Europeans over the age of 65 suffer either sight or hearing loss. Dementia and cognitive impairment steadily rise in prevalence in this same age group to the point where almost one third of Europeans at the age of 90 is affected [4]. Thus, the overlap between sensory and cognitive impairment is substantial and all three impact significantly on each other, resulting in a crucible of ‘multi-morbidity’.

Recent evidence has found that older adults experiencing comorbid cognitive and sensory impairment have greater difficulties in several aspects of their lives compared to individuals with dementia but without sensory impairments [5]. For example, people with comorbid cognitive and sensory problems may have more difficulty in locating themselves using visual or auditory cues and experience higher levels of disorientation and distress, which can lead to agitation, aggression and an increased prevalence of hallucinations and delusions [6]. In addition, such individuals are often more isolated from family interactions, participate less in social activities and hobbies, and are even more marginalised within the community, compared with those who have single morbidity or experience good cognitive or sensory health [7–11]. Such social isolation and disconnection can lead to depression and a more rapid overall decline in function [12]. Furthermore, caregiver burnout and physical exhaustion are amplified due to greater dependency for self-care and other activities of daily living and communication barriers [7]. In spite of this, the gaps and fragmentation in understanding, appropriate assessment, service provision and public awareness are significant across the EU. There is a marked deficit in appropriate detection and management of hearing and visual impairment in up to 94% of people with dementia [13–15]. This results in lost opportunities to foster mental well-being in elderly people [16, 17].

### Meeting the unmet need

In 2014, the European Commission’s Horizon 2020 programme announced a funding call (PHC-22) for research programmes with the aim of ‘promoting mental well-being in elderly Europeans’. Considering the significant negative impact of comorbid cognitive and sensory impairment on the mental well-being of elderly Europeans, addressing this unmet need is an important approach to answering the call. However, straightforward correction of hearing and vision impairments, by means of fitting hearing aids and lenses, is unlikely to succeed in the context of more serious cognitive deficits such as dementia. This is due to the added complexity of concurrent deficits as well as the low rate of access to vision and hearing services in elderly people [8, 18, 19]. Clearly, a more comprehensive approach to improving outcomes in people with dementia and sensory impairment is needed.

A possible solution to this identified need is to provide added ‘sensory support’ to people with dementia who live at home. The objective would be to enhance identification of impairment, improve uptake and adherence of corrective devices and assist in enabling this population to better manage daily life in the context of multiple deficits. It is hoped that through the provision of additional support, the benefits of correcting sensory impairments will be maximised. The ultimate aim of such an enhanced intervention is to improve ‘mental well-being’, which has been defined by the World Health Organization (WHO) as ‘a state of well-being in which the individual realises his or her own abilities, can cope with the normal stresses of life, can work productively and fruitfully, and is able to make a contribution to his or her community’(p10 [20]). ‘Mental well-being’ is also encompassed in the wider definition of health, which states that ‘health is a state of complete physical, mental and social well-being and not merely the absence of disease or infirmity’ (p3 [21]).

### Study protocol

#### Overall aims of the research programme

To understand from different perspectives, the range of support care needs for people with dementia and concurrent hearing and vision impairment and the impact that these impairments have on outcomes such as quality of life and caregiver burden.To develop and field test a complex support care intervention that is theoretically informed and ready to be tested in a subsequent full scale definitive randomised controlled trial (RCT), should the outcomes of this development programme appear positive.

### Primary specific objectives

Step 1: Defining the gapTo scope the gaps in understanding, awareness and service provision for the support care needs of people with dementia and hearing and/or vision impairment using stakeholder input and evidence from the literature;

Step 2: Developing a prototype interventionTo investigate the specific support care needs required by the population in question using a mixed methods approach;To construct a prototype sensory support care package using data integration of the scoping and mixed methods investigations;

Step 3: Refining the prototype interventionTo refine the prototype intervention into a draft intervention ready for field testing;

Step 4: Field testing the draft interventionTo test the acceptability and feasibility of the draft intervention ready for full scale trialling;To ascertain the most appropriate outcome measures to be used in the full trial, including the impact on mental well-being, quality of life, caregiver burden, social connectedness, cognitive functioning and health economic measures.

### Secondary specific objectives

To explore the experiences of people with dementia and hearing and/or vision impairment and those of their significant others.

## Methods/design

Due to the complexity of the intervention and the multiple contexts in which the research will take place, our approach to its development has closely followed the steps outlined by the process of intervention mapping [2]. In order to follow the logical and sequential steps in this process, a mixed methods study design is the most suitable approach. However, in evaluating each applicable ‘dimension of complexity’ (see Table 1), as outlined by the UK’s Medical Research Council (MRC) Guidance on the topic [1], we decided that a modified version of the mapping process was most suited to our needs. Thus, we adopted a non-linear structure to the research programme with both sequential and simultaneous sub-studies using quantitative and qualitative approaches [22].

**Table 1 Tab1:** Description of ‘dimensions of complexity’ in the proposed intervention study as per Medical Research Council Guidance [1]

Dimension	Reason for complexity
Number of and interactions between components within the experimental interventions	Since we anticipate that no two individuals will have the same impairments, the assessment and management of impairment versus functional need will be undertaken by different individuals due to differing skill sets. For example, vision and hearing impairment requiring devices (glasses and hearing aids) will be undertaken by specialist clinicians (optometrists, ophthalmologists and audiologists), whereas the functional ability and environmental context, caregiver assessment and the resulting management strategy will be undertaken by a sensory support worker
Number and difficulty of behaviours required by those delivering or receiving the intervention	Whereas the clinicians will assess and correct hearing and vision impairments according to their standard good practice guidelines, the sensory support worker will undertake newly learned protocols, and will have to choose from a variety of elements, likely within different modules including: vision training, auditory training, caregiver education and training, information delivery, sign-posting and environmental assessment and correction
Number and variability of outcomes	In order to fulfil the remit of improving ‘mental well-being’ in elderly EU citizens, various outcomes need to be captured, including health-related quality of life (QoL), improved functional ability, social connectivity, caregiver factors, attainment of personal goals, as well as more easily quantifiable factors such as cognitive performance, level of depression and other behavioural disturbances.
Degree of flexibility or tailoring of the intervention permitted Implications for development and evaluation	Since no two individuals will have the same degree of cognitive and sensory impairment and functional ability, the intervention will have to be highly tailored and individualised, albeit within the structure of a reproducible, manualised and modular approach in which each person with dementia: caregiver dyad will be offered each module of the intervention package
A good theoretical understanding is needed of how the intervention causes change, so that weak links in the causal chain can be identified and strengthened	The background literature of existing evidence of potential mechanisms, as well as clinical experience, has suggested that each aspect of the intervention can be linked to identifiable intermediate impacts and final outcomes, and can be outlined in a logic model [24]

Importantly, we carefully considered the different weighting of the evidence to be gleaned from each step in the development programme. Thus, in view of the crucial importance of understanding local EU contexts, as well as the paucity of published evidence on which to base quantitative methods, we have chosen to place a greater emphasis on exploratory and qualitative methods, over quantitative approaches. The steps comprising the full research programme are outlined in Fig. 1. The sub-studies included in each of the steps are outlined in Table 1.

**Fig. 1 Fig1:**
[figure not shown]
Flowchart of the sequential and simultaneous steps in the research programme. Person with dementia is abbreviated as PwD

Another important consideration for any intervention, particularly involving behavioural change, is that a theoretical framework be established prior to any development work. The principal aim of the intervention is to improve functional ability and quality of life by supporting sensory function. However, this can only be achieved by changing the behaviour of people with dementia and sensory loss to ensure that they are ‘living better’ as manifested by mental well-being and reduced caregiver burden. We have therefore chosen a comprehensive evidenced-based behavioural model around which the components of the SENSE-Cog intervention will be compiled, the Behaviour Change Wheel [23]. One of the aspects of the Behaviour Change Wheel is the COM-B component, which suggests that the key areas to be addressed to effect behavioural change (‘B’) include *capability* (‘C’), or the individual’s psychological and physical capacity to engage in the activity concerned; *opportunity* (‘O’) or all the factors that lie outside the individual that make the living better with dementia possible; and *motivation* (‘M’), or all those ‘brain processes that energize and direct behaviour, as well as goals and conscious decision-making’ (p5 [23]).

With the Behaviour Change Wheel as a framework, the likely structure of the final intervention will include various components including (1) identifying and correcting any vision or hearing impairment; (2) supporting adherence to the impairment correction with on-going advice and fittings; (3) identifying vision- and hearing-related functional deficits, facilitators and barriers; (4) addressing any identified skill deficit with vision and hearing training for the affected person and their significant other; (5) addressing any identified knowledge deficit with information provision and sign-posting; and (6) improving vision and hearing related functional deficits through home-based environmental aids. The intention is that the sensory support intervention will be highly individualised, be delivered at home, and involve the input of a caregiver or significant other. The overall aim of the intervention will be broad-based and targeted towards improving quality of life, reducing functional disability and increasing social connectedness. Finally, a cornerstone of the entire research programme is the input of patient and caregiver stakeholders by means of interlinking at each step with our ‘Patient and Public Voice’ (PPV) team.

### Aspects of intervention complexity to consider in designing the research programme

Our early scoping work in the literature and ‘gap analysis’ in our Expert Reference Group (ERG) identified several dimensions of complexity which need to be addressed in the development of the intervention. These are outlined in Table 2:

**Table 2 Tab2:** Sub-studies included in the process of developing a complex intervention

Sub-study	Aim	Participants	Design	Setting	Data analysis
Expert Reference Group	To scope expert opinions on gaps in understanding of the support care needs and potential solutions for people with cognitive and sensory problems	Expert professionals from several disciplines (audiology, vision science, ophthalmology, optometry, health psychology, social work, occupational psychology, occupational therapy and social gerontology)	Three components: 1. Discussion of assessment and management of prototypical cases 2. Analysis of implementation of existing complex dementia trials 3. A modified Delphi to establish a list of support care needs	A two-day meeting in Athens, Greece	Prototypical case discussions will be transcribed and subject to content analysis
Focus group A	To scope the needs of people with dementia and sensory impairment	Three focus groups (*n* = 8 per group) will be conducted with people with dementia and sensory impairment, their study partners and professionals in three sites	Focus groups will be used to discuss support care needs of this population	Three focus groups will take place in each of three sites (total of nine groups): Manchester, Nicosia and Bordeaux	Conversations will be transcribed using MAXQDA software and subjected to content analysis. Cross-site differences will be explored within the analysis of these discussions
Needs analysis survey	To scope the support care needs of people with dementia and sensory impairment	People with dementia and sensory impairment and their study partner. Three sites will recruit between 30 and 40 dyads each	A series of questionnaires will be used to scope the needs, quality of life, degree of impairment, caregiver burden, mental and physical health of participants	Manchester will be the site for 40 participant dyads; Nicosia and Bordeaux will each recruit 30 dyads (total of 100 dyads).	Regression analyses will be used to explore the relationships between variables
Focus group B	To receive feedback on a draft intervention	Three focus groups (*n* = 8 in each group) will be run using professionals, people with dementia, and their study partners	Information from the preceding stages will be integrated to inform a draft intervention, which which will be presented to participants for comment and feedback	These will be the same three sites that participated in focus group A; however, the participants may differ between the two focus groups	As with focus group A, discussions will be transcribed and analysed using content analysis
Field Trial of draft intervention	To trial a ‘sensory support’ intervention for people with dementia and sensory impairment	Eight participant dyads (people with dementia and sensory impairment and their study partners) in each of three sites	A 12-week ‘sensory support’ intervention involving correction of hearing/vision impairments, communication training, ‘sensory proofing’ the home environment, and signposting to relevant services. Baseline and follow-up data will be collected along with process measures and reflective diaries	Three sites will recruit a total of 24 participant dyads: Manchester, Nicosia, and Bordeaux	Data from the diaries and verbatim data from the interviews will be analysed using a summative content analysis. Quantitative parametric data will be analysed using two-tailed *t* tests, with 95% CIs. Effect sizes using the Hedges’ g formula (similar to Cohen’s d), appropriate for small sample sizes will be calculated. Due to the small sample, only a large *p* value, 0.2, will be an indication of effect. The score distributions will be examined for degree of variability and ceiling and floor effects. Participants’ subjective report of the overall helpfulness of the intervention will give an initial impression of efficacy. An initial impression of treatment efficacy will be obtained by examining before and after-intervention measures of a variety of rating scales of dementia-related outcomes

At the end of this part of the research programme, we will have determined the following:What method we will use to assess participants’ (a) level of hearing and vision impairment and (b) range of functional needs in a home-based setting, in order to tailor the intervention to their specific needs.What the individual components (e.g. modules) of intervention will be.How the intervention will be implemented (e.g. duration, frequency and delivery of each component).What causal assumptions about mechanisms of producing change in a home-based setting will be made.How the intervention will work in the context of different EU settings.

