### Step 4: Field testing the draft intervention

The final step in the programme will be to field test the draft sensory support intervention with a participant population representative of the group who will participate in the subsequent RCT of the intervention, should the results of the field test be positive.

*Objective:* The field study will have three objectives: (1) to undertake a process evaluation of the components and implementation of the intervention, including reach and fidelity issues, acceptability and tolerability of the intervention for participants as well as the contextual issues; (2) to examine the operational aspects of a future trial design, including recruitment and retention and training methods and materials; and (3) to explore the feasibility and face validity of potential outcome measures for the future trial. As the field trial comprises a complex, multi-faceted study, it is described elsewhere in detail ([name], et al. Improving hearing and vision in dementia: protocol for a field trial of a new intervention, in submission). The current description is comprised of a brief overview of the field trial in the context in which it has been developed.

*Method:* This will be an open-label feasibility study in people with dementia and sensory impairments and their caregivers in each of three clinical sites. There will be no control group. Participants, researchers and sensory support workers will not be masked to intervention assignment and all participants and their caregivers will receive either the full draft intervention package or certain components of the package decided a priori. Whether or not the individual receives the full intervention or a reduced version will depend on their availability, interest and need for support in certain areas.

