*Participants:* The study population for the field trial will reflect the intended study population of the potential large-scale RCT as closely as possible and will include two groups of participants, all ≥ 60 years and living at home: (1) those with a diagnosis of dementia^1^ mild-to-moderate stage (Montreal Cognitive Assessment ≥ 12 [45]), and sensory impairment; and (2) their caregivers/significant others who will act as ‘study partners’. Hearing and vision function will be classified according to a priori established criteria of impairment. Caregivers or significant others will be included if they have a personal relationship with the participant, such as a family relation, friend or neighbour and can provide information about the participant’s condition and are willing to take part in the study themselves. Any participant unlikely to comply with follow-up (e.g. due to an unstable medical condition or having an urgent need for a sensory intervention) will not be included in the study.

*Sample size*: In this feasibility study, a formal power calculation will not be undertaken as no inferential analyses of efficacy are planned. Instead, we will enrol 24 participant:caregiver dyads across three clinical sites (8 dyads per site) which should give sufficient opportunity to extract the information needed from the study and fulfil the objectives.

*Setting:* The study will take place in clinic settings and participants’ own homes in each of the three study sites: Manchester, Nicosia and Bordeaux.

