*Study procedures:* The procedures are summarised in Fig. 2. Briefly, the study will take place over a period of three months with a series of interventions offered by professionals (opticians and audiologists), sensory support workers (SSW), and researchers undertaking the outcome assessments. Following recruitment, participants will be required to provide informed consent to participate. In order to overcome potential issues with consent presented by functional and sensory impairments, the researcher will be able to fill in the consent form on behalf of the individual and countersign to confirm that verbal consent has been provided. Following the signing of consent, potential participants will be screened for suitability to be included in the study. Screening will entail brief checks of hearing (using the SIEMENS HearCheck), vision (using the PEEK acuity smartphone application) and cognition (using the MoCA). For those who pass screening, a clinical assessment of vision and hearing status will be arranged. Vision status will include refraction, visual acuity, fields and contrast sensitivity. Hearing status will include otoscopy, tympanometry and pure tone audiometry. If surgical or invasive corrections are required (e.g. for cataracts or macular degeneration), the participant will be withdrawn from the study. If non-surgical sensory corrections or improvements can be provided with devices (hearing aids and/or lenses), these devices will be offered and fitted. Fitting and uptake of the new devices will be supported by the SSW who will visit the participant at home. Once impairments have been optimally corrected, a home-based assessment of vision and hearing functional ability will be undertaken in order to assess the specific support care needs of the participant and their caregiver. Based on the needs identified, a sensory support package will be offered to the dyad, based on the COM-B framework outlined above [23]. The specific components (e.g. content of each module) and manner of implementation (e.g. frequency and duration of support visits) will be determined from the intelligence gathered in steps 1 to 3 of the research programme. The final protocol outlining the study procedures and the draft intervention to be field tested will be prepared at the end of step 3. A researcher will undertake a series of process evaluations at each step of the protocol in order to ascertain such outcomes as feasibility, tolerability, acceptability and fidelity and reach of the intervention. The evaluations will involve participant diary keeping, direct researcher observations of visits, participant satisfaction scales, and SSW and researcher feedback. At the end of the intervention, each participant:caregiver dyad will participate in a 1–2 h semi-structured interview with the researcher to give feedback on the intervention components and implementation. A similar evaluation will be undertaken to ascertain successful aspects of trial procedures and outcome measures used. The outcomes to be explored will include measures of quality of life, mood, well-being, cognitive and functional ability, caregiver indices (e.g. burden, stress, well-being, and mood) and health economic measures.

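### Table 2 treats p = 0.2 on uncontrolled before/after t tests as a sign of effect in the field trial, while Step 4 says no inferential efficacy analysis is planned

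*Protocol article*

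**What the plan says.** The field trial enrols eight dyads at each of three sites, all offered the intervention. Three places in the protocol article bear on how its outcome scales will be read.

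- **Table 2, field trial row, data-analysis column.** "Quantitative parametric data will be analysed using two-tailed *t* tests, with 95% CIs". The cell then sets the threshold: "Due to the small sample, only a large *p* value, 0.2, will be an indication of effect". It closes with: "An initial impression of treatment efficacy will be obtained by examining before and after-intervention measures of a variety of rating scales of dementia-related outcomes".
- **Step 4, Method and Sample size.** "There will be no control group", and "a formal power calculation will not be undertaken as no inferential analyses of efficacy are planned".
- **Step 4, Study procedures.** The outcomes to be explored are "measures of quality of life, mood, well-being, cognitive and functional ability, caregiver indices (e.g. burden, stress, well-being, and mood) and health economic measures". No number of tests is given and none of these outcomes is singled out.

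The Analyses paragraph of Step 4 is descriptive as regards quantitative data (recruitment, retention, tolerability, reaction to the sessions) and mentions neither t tests nor a 0.2 threshold. The Dissemination section lists early efficacy results among the scientific outputs.

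**The concern.** A p-value threshold at which an outcome counts as showing effect is an inferential efficacy rule, whatever it is called. Table 2 contains one; the sample-size paragraph says there is none and uses that as the reason for not calculating power. Both cannot stand.

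The reason offered for the loose threshold, the small sample, does not support it. Raising the threshold makes a signal easier to obtain but no more trustworthy. Applied to several scales in an uncontrolled study, the rule will often pick out an outcome by chance. It will also pick out any change that would have happened without the intervention. Because efficacy results are to be reported, such a signal could be published as an early indication that the intervention works.

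**Working it through.** **Reading of the rule.** Taken literally, the sentence says that a large p value signals effect. The evident meaning is a liberal threshold, so p of 0.2 or less is used below.

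**Inputs.** From the article: n = 3 × 8 = 24 dyads (this reproduces the stated sample size; no power figure is stated), two-sided threshold 0.2, 95% intervals, before/after comparison, no control group. Assumed: all 24 dyads complete, and changes are analysed within person. The number of outcomes k is also assumed. The named domains count to about 10: quality of life, mood, well-being, cognition, function, four caregiver indices and health economics. As four of these come from an illustrative list and t tests are limited to parametric data, k is varied from 5 to 15.

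**Step 1: the 0.2 rule against the 95% interval.** In units of the SD of change, with 23 degrees of freedom:

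- Change at which p = 0.2: t(0.90) / √24 = 1.319 / 4.899 = 0.27.
- Half-width of the 95% interval: t(0.975) / √24 = 2.069 / 4.899 = 0.42.
- Interval at p = 0.2: 0.269 - 0.422 = -0.15 to 0.269 + 0.422 = 0.69.

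Any mean change between 0.27 and 0.42 SD would meet the rule while its planned interval includes zero. The interval that matches a 0.2 threshold is an 80% one.

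**Step 2: chance of at least one signal when nothing changes.** For independent tests the probability is 1 - 0.8^k in either direction and 1 - 0.9^k in the favourable direction only. For k = 10: 1 - 0.8^10 = 89% and 1 - 0.9^10 = 65%. For correlated outcomes I simulated k equicorrelated paired t tests with n = 24 (40,000 runs per cell).

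| Correlation | k = 5: any / favourable | k = 10: any / favourable | k = 15: any / favourable |
|---|---|---|---|
| 0 (formula) | 67% / 41% | 89% / 65% | 96% / 79% |
| 0.3 | 63% / 34% | 85% / 50% | 93% / 59% |
| 0.5 | 58% / 29% | 76% / 41% | 86% / 48% |
| 0.7 | 49% / 24% | 63% / 32% | 70% / 36% |

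The expected number of chance signals among 10 outcomes is 10 × 0.2 = 2, whatever the correlation.

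**Step 3: no control group.** If scores shifted by an assumed 0.2 SD of change for reasons other than the intervention, the noncentral t distribution (n = 24, noncentrality 0.2 × 4.899 = 0.98) gives p of 0.2 or less in 39% of tests on a single outcome, against 20% with no shift.

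**The case against.** The best defence is that this is a 24-dyad open-label feasibility study whose three objectives concern process, operations and the suitability of outcome measures, not efficacy. Table 2 itself speaks of a first impression, liberal thresholds are sometimes used for screening in pilot work, and a 95% interval that includes zero would show readers how weak a signal is. The article also calls its account of the field trial a brief overview and points to a separate protocol.

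Much of this limits the point without removing it. The cell presents 0.2 as evidence of effect and not as a screening rule with a stated error cost, and a separate protocol cannot cure two opposing statements in this article.

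Three stronger readings are tempting and are not supported:

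- *A false signal is almost guaranteed.* The number of tests is not stated and the outcomes are plausibly correlated. Even with 10 independent tests the figure is 89%, and it passes 95% only at about 14 (1 - 0.8^14 = 95.6%). For a favourable signal it is far lower.
- *The 0.2 rule decides whether the full trial goes ahead.* The Analyses paragraph of Step 4 bases reasons for not proceeding on process and operational findings. The overall aims and the opening of Step 4 do make the full trial depend on positive results, but neither defines positive by a p value.
- *The missing multiplicity policy and the unspecified form of Hedges' g are errors.* These are details that an article may leave to the fuller field-trial protocol. A paired reading is the natural one for before/after data without a control group.

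**Conclusion.** The contradiction between Table 2 and the sample-size paragraph of Step 4 is real and lies within this one document. The 0.2 rule is also inconsistent with the 95% intervals beside it. If it were followed, a chance signal would be likely: across 5 to 15 outcomes and correlations of 0 to 0.7, about 49% to 96% in either direction and about 24% to 79% in the favourable direction. These figures rest on an assumed number of tests, equal correlations, complete data and no true change. The consequence is an unsound efficacy statement in the planned report, not a formally wrong progression decision. It should be fixed, but it does not undermine the feasibility study itself.

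**What to change.** In the field trial row of Table 2, delete the p = 0.2 sentence and any reading of the t tests as evidence of effect, so that the cell agrees with the sample-size paragraph. For each measure, report the mean before/after change with its confidence interval and the SD of change, labelled as descriptive information for planning the full trial, and call no outcome effective. If a more liberal interval is wanted, add an 80% interval alongside the 95% one. The report listed under Dissemination should present these estimates in the same terms.

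The cost is the wording of one table cell; no further data are needed. The sponsor gives up the option of claiming a sign of effect from this study.
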